#### 3.2.3 Part two - secondary endpoints

- 1) The % uptake (of total injected)  $^{89}\text{Zr}$ -cetuximab in liver lesions as measured in ROI's corrected for background levels.
- 2) [18F]-FDG PET measurements ( $\text{SUV}_{\text{max}}$ ) before and after 4 weeks of treatment with cetuximab.
- 3) Grade of skin toxicity as measured by predefined criteria (see below).

#### 3.2.1 Other study parameters

- 4) Serum magnesium levels before and during treatment.
- 5) EGFR saturation with cetuximab in skin samples.
- 6) Kinase activity in skin samples before and after treatment with cetuximab.
- 7) Pharmacokinetics of  $^{89}\text{Zr}$ -cetuximab.

## 4 Patient selection criteria

### 4.1 Inclusion criteria

Subjects are eligible if they meet the following criteria:

- Advanced colorectal adenocarcinoma
- Subjects must have been treated according to standard care with a fluoropyrimidine (e.g. fluorouracil or capecitabine), irinotecan, and oxaliplatin or had contra-indications to treatment with these drugs.
- Age  $\geq 18$  years.
- Histological or cytological documentation of cancer is required.
- Tumor material must be tested wild type for the K-Ras gene.
- Subjects have at least one measurable lesion outside the liver. Lesions must be evaluated by CT-scan or MRI according to Response Evaluation Criteria in Solid Tumors (RECIST 1.1).
- ECOG Performance Status of 0, 1 or 2
- Adequate liver and renal functions as assessed by the following laboratory requirements to be conducted within 7 days prior to screening:
  - Total bilirubin  $\leq 1.5$  times the upper limit of normal
  - ALT and AST  $\leq 2.5$  times upper limit of normal ( $\leq 5$  times upper limit of normal for subjects with liver involvement of their cancer)
  - Serum creatinin  $\leq 1.5$  times upper limit of normal or a calculated creatinin clearance  $\geq 50$  ml/min
- Signed informed consent must be obtained prior to any study specific procedures.

### 4.2 Exclusion criteria

Subjects who meet the following criteria at the time of screening will be excluded:

- Previous exposure to an anti-EGFR therapy
- Significant skin condition interfering with treatment
- Insulin dependency
- Pregnant or breast-feeding subjects. Women of childbearing potential must have a negative pregnancy test performed within 7 days of the start of treatment. Both men and women enrolled in this trial must agree to use adequate barrier birth control measures (e.g., cervical cap, condom, and diaphragm) during the course of the trial. Oral birth control methods alone will not be considered adequate on this study, because of the potential pharmacokinetic interaction between study drug and oral contraceptives. Concomitant use of oral and barrier contraceptives is advised. Contraception is necessary for at least 6 months after receiving study drug.
- Concurrent anticancer chemotherapy, immunotherapy or investigational drug therapy during the study or within 4 weeks of the start of study drug.
- Radiotherapy to the target lesions during study or within 4 weeks of the start of study drug. Palliative radiotherapy will be allowed.
- Major surgery within 28 days of start of study drug.
- Substance abuse, medical, psychological or social conditions that may interfere with the subject's participation in the study or evaluation of the study results.
- Any condition that is unstable or could jeopardize the safety of the subject and their compliance in the study.

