**Intervention:** Patients will be treated with cetuximab. For pharmacodynamic purposes PET-imaging with Zr-labelled cetuximab will be performed. In addition, two [18F]-FDG PET-CT will be performed to explore early response. Patients will undergo blood sampling and two skin biopsies for pharmacodynamic purposes of Zr-labelled cetuximab and kinase activity profiles, respectively.

**Main study objective/endpoint:** The main objective of the first part of the study is the demonstration of Zr-cetuximab uptake in non-hepatic tumor lesions. The main objective of the second part is the association between Zr-cetuximab uptake in non-hepatic tumor lesions and treatment outcome.

**Nature and extent of the burden and risks associated with participation, benefit and group relatedness:** Upon enrolment in this study, patients will be asked to undergo two skin biopsies during treatment. During therapy, follow-up will include standard laboratory analysis, immuno-PET-CT and [18F]-FDG PET-CT on regular visits to the outpatient clinic. Side effects of the medication and adverse events as a consequence of the skin biopsies may occur. The radiation exposure is acceptable and requires no shielding after injection of Zr-labelled cetuximab. Patients may benefit from disease regression or stabilization as cetuximab has proven clinical benefit in this patient population.

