### 5.2 Pre-study evaluation and follow-up

Upon informed consent for participation in this trial, baseline evaluations except imaging are to be conducted within 14 days prior to start of protocol therapy. [18F]-FDG PET and CT and/or MRI will be done  $\leq 4$  weeks prior to start of therapy.

Five patients will be asked to undergo 3 additional PET scans (after the  $^{89}\text{Zr}$ -cetuximab dose) and 3 simultaneous venous blood samples in order to study pharmacokinetics of  $^{89}\text{Zr}$ -cetuximab in more detail.

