| pharmacokinetics                |          | 0-2h, day 2,3,4 and 7
1h and day 4 or 7     |                                                                         |              |

**Chemistry panel:** Na, K, Ca, Mg, Alb, creatinin, bilirubin,  $\gamma$ GT, AF, ASAT, ALAT, LDH.

**Hematology:** Hb, Ht, WBC, ANC, Platelets

**Radiology:** MRI or CT images will be required within 4 weeks before start, every 2 months during the first year of treatment and thereafter every 3 months until progressive disease. CT scans or MRI scans will be performed according to standard procedures. The radiologist will review any responses using RECIST 1.1 independently from the investigator.

**18FDG-PET:** scans will be required within 4 weeks before start and 4 weeks after start.

**Immuno-PET-CT scan:** The first five patients will be asked to undergo in total 5 immuno-PET scans and 5 simultaneous venous blood samples at 0-2h, day 2,3,4 and 7 after administration of Zr -cetuximab in order to study pharmacokinetics of Zr -cetuximab in more detail. The following patients will undergo in only 2 immuno-PET scans, at 0-2h and 4 or 7 days after Zr –cetuximab administration.

Follow up will last till progressive disease and/or death of the patient. In the case of progressive disease, the choice of any following line palliative chemotherapy is at the discretion of the investigator.

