### **10.3 Benefits and risks assessment**

#### **10.3.1 Risks**

Use of positron emitting radionuclides means exposure to ionizing radiation. The total effective dose of one administration of Zirconium-89 MAb will be about 20 mSv. Low-dose CT will deliver 3 mSv per CT. [18F]-FDG yields a radiation dose of 3.3 mSv for 185MBq.

When considering the justification of application, a risk to benefit analysis has to be performed. ICRP-62 provides a model for this. According to this model, the risk level corresponds to “moderate”, while the social benefit corresponds to “substantial”.

After injection of the conjugate no shielding is required, and the patient can go directly home without further limitations. The risks of cetuximab are well-known as this drug is used in routine clinical practice (see above for detailed description). The first 6 months after the study both males and females are advised to prevent pregnancy.

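### The only dated pregnancy test is tied to the start of treatment, so the study's baseline FDG-PET can precede it by three weeks or more

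*Protocol*

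**What the plan says.** Section 4.2 lists pregnancy as an exclusion and introduces the list with "Subjects who meet the following criteria at the time of screening will be excluded". The one dated check follows in the same bullet: "Women of childbearing potential must have a negative pregnancy test performed within 7 days of the start of treatment".

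The imaging windows are set elsewhere. Section 5.2 says that "baseline evaluations except imaging are to be conducted within 14 days prior to start of protocol therapy", and then gives FDG-PET and CT or MRI a limit of 4 weeks before therapy. Footnote 4 to Table 1 repeats this for FDG-PET: "scans will be required within 4 weeks before start and 4 weeks after start".

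The FDG scans belong to the research. Under the intervention heading the Summary says: "In addition, two [18F]-FDG PET-CT will be performed to explore early response". They also serve a secondary objective (3.1.4) and a secondary endpoint (3.2.3).

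Table 1 has no row for a pregnancy test. The chemistry panel in its first footnote begins "Na, K, Ca, Mg, Alb, creatinin, bilirubin" and contains no pregnancy marker, and neither does the hematology panel. Section 5.5.4 (FDG-PET) and section 10.3.1 (risks) do not mention a test.

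**The concern.** A pregnancy test protects a possible fetus only if it comes before the exposure. Section 4.2 dates the test from the start of cetuximab, but the first study exposure to radiation can be the baseline FDG-PET, which may be up to 4 weeks earlier. If the two windows are followed as written, the scan can come first and the test later.

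What is at stake is patient safety. A woman with an unrecognised pregnancy could receive research radiation before the protocol's own check would have found the pregnancy. Endpoints, sample size and analysis are untouched.

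**Working it through.** The protocol gives no figure to reproduce. The check compares two windows by day count, with the start of treatment as day 0 and counting the days before it.

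**Inputs**
- Pregnancy test: within 7 days of start (4.2), so the earliest valid day is -7. If the wording is read as 7 days on either side of start, the earliest valid day is still -7.
- Baseline FDG-PET: up to 4 weeks before start (5.2; Table 1, footnote 4), so days -28 to -1, which is 28 days.
- Other baseline evaluations: within 14 days before start, imaging exempted (5.2).
- Doses (10.3.1): 3.3 mSv for 185 MBq of FDG; for the CT, "Low-dose CT will deliver 3 mSv per CT"; about 20 mSv for the zirconium-89 antibody.

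**Scan days that precede any valid test**
- Days -28 to -8: 28 - 7 = 21 days.
- Share of permitted scan days: 21/28 = 75%.

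**Interval from scan to test**
- Scan on day -28, test on its earliest valid day: 28 - 7 = 21 days.
- Scan on day -8, test on its earliest valid day: 8 - 7 = 1 day.
- Scan on day -28, test on day -1: 28 - 1 = 27 days.

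A test done on the scan day anywhere from day -28 to day -8 would be too early to count under 4.2. On days -7 to -1 a valid test can come before the scan, but no text requires that order.

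**Sensitivity to other readings**
- Test treated as an ordinary baseline evaluation, allowed from day -14 (more lenient than 4.2): days -28 to -15 still precede it, which is 14 of 28 days, or 50%.
- Scan held to the Table 1 baseline column (weeks -2 to 0) instead of the 4 weeks in the footnote: days -14 to -8 still precede a valid test, which is 7 of 14 days, or 50%.

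The gap narrows under either reading but does not close.

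**Patient dose from the early scan**
- FDG alone: 3.3 mSv.
- FDG as PET-CT: 3.3 + 3 = 6.3 mSv. This assumes that the stated low-dose CT dose applies to the FDG scan. Section 5.5.2 specifies the low-dose CT for the immuno-PET only, and 5.5.4 allows either PET or PET-CT.

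The baseline CT has the same 4-week limit. It is left out because it may be standard care.

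**The case against.** The strongest reply is that pregnancy is not judged only at the start of treatment. Section 4.2 applies its exclusions at screening, and enrolled patients must agree to barrier contraception during the trial. On this view the 7-day test is a further confirmation, sensibly placed just before the larger hazards: cetuximab itself and the labelled antibody at about 20 mSv. A single early test would leave up to four weeks unverified before those exposures.

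Much of this stands. A test close to dosing is right and should stay. But the screening exclusion prescribes no test, and contraception from enrolment does not detect a pregnancy that already exists. These safeguards narrow the gap without closing it.

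A second reply is that 5.5.4 commits the FDG studies to a published imaging guideline, which may require a check at the scanner. That cannot be judged from the protocol. It limits what can be said about actual practice, but not what can be said about the order of the protocol's own windows.

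A third reply is that 75% is a share of permitted calendar days, not of scans or of risk. This is correct: the protocol does not say when scans will be booked, so the figure describes only what is allowed.

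**Conclusion.** The concern holds, as a minor patient-safety point. The protocol's only dated pregnancy test is tied to treatment, and a baseline FDG-PET on days -28 to -8 comes before any test that meets 4.2. The day count is firm and survives the alternative readings of the windows.

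The practical size is small. It concerns only women of childbearing potential among at most 38 patients in a third-line setting. The protocol gives neither their number nor a fetal dose; that they will be few is an assumption. The exposure before the test is one scan of 3.3 mSv, or about 6.3 mSv under the CT assumption. Whether local practice or the cited guideline already adds a check at the scanner is unknown.

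**What to change.** Reword 4.2 so that women of childbearing potential need a negative pregnancy test before the baseline FDG-PET and a negative test within 7 days before the start of treatment. One test can serve both purposes if the scan is booked after it within the same 7 days; otherwise two tests are needed. The sponsor can choose either route. Saying before the start, instead of only within 7 days of it, also removes the reading under which a test after dosing would count.

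Add a pregnancy-test row to Table 1, with a footnote placing the test ahead of the FDG-PET.

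The cost is one sentence in 4.2, one row in Table 1 and, for the few women affected, a tighter scan booking or one extra inexpensive test.

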## 5 Trial design

### 5.1 Participant recruitment

Patients will be included from the VUMc Medical Oncology Department and the Internal Medicine Department of the Medical Centre of Hoofddorp (Spaarne Ziekenhuis) in an outpatient setting. As on a monthly basis five of the aforementioned patients are diagnosed, approximately three patients per month are expected to be included. Therefore, accrual accomplishment is estimated within one year.

### 5.2 Pre-study evaluation and follow-up

Upon informed consent for participation in this trial, baseline evaluations except imaging are to be conducted within 14 days prior to start of protocol therapy. [18F]-FDG PET and CT and/or MRI will be done  $\leq 4$  weeks prior to start of therapy.

Five patients will be asked to undergo 3 additional PET scans (after the  $^{89}\text{Zr}$ -cetuximab dose) and 3 simultaneous venous blood samples in order to study pharmacokinetics of  $^{89}\text{Zr}$ -cetuximab in more detail.

**Table 1 Standard evaluation, laboratory tests and follow-up**

|                                 | Baseline | Start treatment                                | From week 5                                                             | End of study |
|---------------------------------|----------|------------------------------------------------|-------------------------------------------------------------------------|--------------|
| Week                            | - 2 to 0 | 1,3 and 5                                      | every 4 wks                                                             |              |
| History                         | X        | X                                              | X                                                                       | X            |
| Phys. exam                      | X        | X                                              | X                                                                       | X            |
| Skin biopsy                     | X        | After 3-4 wks of treatment                     |                                                                         |              |
| Toxicity                        | X        | X                                              | X                                                                       | X            |
| Chemistry           | X        | X                                              | X                                                                       | X            |
| Hematology          | X        | X                                              | X                                                                       | X            |
| Tumor marker (if applicable)    | X        | every 4 wks                                    | every 4 wks                                                             | X            |
| Tumor measurements  | X        |                                                | every 2 mths for the first year, every 3 mths after 1 year of treatment | X            |
| 18FDG-PET           | X        |                                                | 4 wks                                                                   |              |
| Immuno PET-CT       |          | 0-2h, day 2, 3, 4 and 7
0-2h and day 4 or 7 |                                                                         |              |
| pharmacokinetics                |          | 0-2h, day 2,3,4 and 7
1h and day 4 or 7     |                                                                         |              |

**Chemistry panel:** Na, K, Ca, Mg, Alb, creatinin, bilirubin,  $\gamma$ GT, AF, ASAT, ALAT, LDH.

**Hematology:** Hb, Ht, WBC, ANC, Platelets

**Radiology:** MRI or CT images will be required within 4 weeks before start, every 2 months during the first year of treatment and thereafter every 3 months until progressive disease. CT scans or MRI scans will be performed according to standard procedures. The radiologist will review any responses using RECIST 1.1 independently from the investigator.

**18FDG-PET:** scans will be required within 4 weeks before start and 4 weeks after start.

**Immuno-PET-CT scan:** The first five patients will be asked to undergo in total 5 immuno-PET scans and 5 simultaneous venous blood samples at 0-2h, day 2,3,4 and 7 after administration of Zr -cetuximab in order to study pharmacokinetics of Zr -cetuximab in more detail. The following patients will undergo in only 2 immuno-PET scans, at 0-2h and 4 or 7 days after Zr –cetuximab administration.

Follow up will last till progressive disease and/or death of the patient. In the case of progressive disease, the choice of any following line palliative chemotherapy is at the discretion of the investigator.

### 5.3 Withdrawal of individual subjects

A patient will be discontinued from the study therapy under the following circumstances:

- evidence of progressive disease
- upon patient's request for any reason
- unacceptable toxicity

Patients who withdraw their informed consent within the first 6 weeks while no medical need for withdrawal exists can be replaced at the discretion of the investigator's team. If during screening a patient's condition deteriorates and the patient becomes unfit for treatment, the patient will be replaced.

Patients withdrawn from treatment for any reason except progressive disease will continue follow up as specified above unless the patient declines.

### 5.4 Treatment

#### 5.4.1 Treatment with cetuximab

##### Unlabelled cetuximab infusion

Unlabelled cetuximab will be given intravenously in a biweekly schedule with 500 mg per square meter of body surface area as initial and maintenance dose. An antihistamine will be given before each dose of cetuximab. Treatment will be continued until death, in the absence of the occurrence of unacceptable adverse events, tumor progression, worsening symptoms of the cancer, or request by the patient. The infusion will take place at the outpatient department of Medical Oncology of the VUmc. Afterwards, the patient is moved to the department of Nuclear Medicine & PET research of the VUmc where the infusion of the labeled part of the cetuximab will take place within two hours after administration of the unlabelled cetuximab.

##### Zr-abelled cetuximab infusion

For the labeled Zr-cetuximab injection, the infusion line inserted for the unlabelled cetuximab will be used. Zr-cetuximab will be injected as a bolus of 20mL followed by 10mL physiologic saline flushing. All relative times after treatment have to be understood with respect to the end of this infusion. This time will be considered as study time "0:00". (see SECTION 6 Investigational Medicinal product for details regarding Zr –cetuximab).

#### 5.4.2 Standard toxicity management of cetuximab

As a class of targeted drugs, EGFR inhibitors do not show many of the severe side effects commonly observed with cytotoxic chemotherapy except for skin toxicity. In most patients, this skin rash exhibit some degree of spontaneous partial improvement during therapy and it generally resolves completely without scarring following cessation of EGFR inhibition. In case of  $\geq$  grade 3 toxicity follow table 2 for treatment adjustment.

Other side effects include hypersensitivity reactions. After appropriate measures have been taken treatment will be continued at a decreased infusion rate in case of a mild hypersensitivity reaction

(CTC 4.0 grade  $\leq 2$ ). In case of hypersensitivity reactions exceeding grade 2 treatment will be stopped (table 2).

Also reversible electrolyte deficiencies, dyspnoea, fatigue, asthenia and diarrhea have been reported, none exceeding grade 3 toxicity.

**Table 2** Treatment adjustment to specific toxicities

| Toxicity                                       | Severity                                                          | Dose adjustment/other measures                                                                                                                                                                                                                                                                                                                                           |
|------------------------------------------------|-------------------------------------------------------------------|--------------------------------------------------------------------------------------------------------------------------------------------------------------------------------------------------------------------------------------------------------------------------------------------------------------------------------------------------------------------------|
| Skin rash
Graded according to Table 3       | Grade 1 and grade 2                                               | No dose adjustment required.
Standard acne treatment can be started                                                                                                                                                                                                                                                                                       |
|                                                | Grade $\geq 3$ as graded                                          | Delay further treatment until skin rash has ameliorated to grade $< 3$  ,
Restart at maintenance dose                                                                                                                                                                                                                                                     |
|                                                | Grade $\geq 3$ persists $> 3$ weeks after dose delay of cetuximab | Subjects must be withdrawn from the treatment.                                                                                                                                                                                                                                                                                                                           |
| Hypersensitivity
Graded according to CTC4.0 | Grade 1                                                           | Decrease the cetuximab infusion rate by 50% and monitor closely for any worsening.                                                                                                                                                                                                                                                                                       |
|                                                | Grade 2                                                           | Stop cetuximab infusion.
Administer bronchodilators, oxygen, etc. as medically indicated.
Resume infusion at 50% of previous rate once allergic/hypersensitivity reaction has resolved or decreased to Grade 1 in severity, and monitor closely for any worsening                                                                                                  |
|                                                | Grade 3 or grade 4                                                | Stop the cetuximab infusion immediately and disconnect infusion tubing from the subject.
Administer epinephrine, broncho- dilators, antihistamines, glucocorticoids, intravenous fluids, vasopressor agents, oxygen, etc., as medically indicated.
Subjects must be withdrawn immediately from the treatment and must not receive any further cetuximab treatment. |

Standard acne treatment is allowed and may provide some benefit. Treatment according to the Nederlands Huisartsen Genootschap will be allowed using topical applications of benzoylperoxide hydrogel 5% (50 mg/g) once daily or tretinoïne (Vitamine A acid) crème 0.05% (0.5 mg/g), once daily in the evening. In the absence of improvement, clindamycin hydrochloride lotion 1% (10 mg/ml), once daily in the morning may be applied. Ultimately, switching to doxycycline while continuing tretinoïne or benzoylperoxide therapy is allowed but consultation of a dermatologist is strongly recommended in this case.

In case of severe skin toxicity (grade  $\geq 3$ ) treatment will be withheld and dermatologic therapy will be started (standard acne treatment, see above). Once skin toxicity improves ( $\leq$  grade 2), cetuximab will be restarted at maintenance dosage level. In case of persistent severe skin toxicity, cetuximab will be discontinued.

